## **1. OBJECTIVES**

### **1.1 Primary Objectives**

- 1.1.1 To assess the safety and characterize the toxicity of Helixor® M mistletoe extract administered intravenous (IV) in patients with advanced solid tumors.
- 1.1.2 Identify the maximum tolerated dose (MTD)

### **1.2 Secondary Objectives**

- 1.2.1 To measure tumor marker kinetics in patients receiving treatment.

### **1.3 Exploratory Objectives**

- 1.3.1 To estimate progression-free survival (PFS) and time to progression (TTP) in patients treated with Helixor® M mistletoe extract using RECIST 1.1 and irRC.
- 1.3.2 To collect peripheral blood mononuclear cells (PBMCs), serum, and plasma to explore potential therapeutic targets, biomarkers, and predictors of treatment response (PFS and best overall response).
- 1.3.3 To assess tumor burden dynamics using exploratory circulating biomarkers in serial collections of sera and plasma at baseline and throughout treatment.
- 1.3.4 To collect pre and post-treatment whole blood to evaluate germline mutations in circulating DNA that may correlate with clinical benefit (PFS and best overall response).
- 1.3.5 To determine changes in cytokine production by peripheral blood mononuclear cells (PBMC) as indicated by interleukin 2 [IL-2], interleukin 6 [IL-6], interleukin 8 [IL-8], interleukin 12 [IL-12], and interferon- gamma [IFN-γ].

## 2. BACKGROUND

The treatment of cancer with mistletoe extracts were first introduced by Rudolf Steiner in the 1920s. However, the use of mistletoe for its medicinal properties to treat numerous human ailments dates back several thousand years. Commercially available mistletoe extracts are prepared from *Viscum album* Linnaeus (*Viscum album* L. or European mistletoe). *Viscum album* L. is a semi-parasitic plant that grows on several different types of trees. The extracts derived from mistletoe contain numerous ingredients in varying concentrations depending on the species of the host tree (e.g. apple, elm, oak, pine, birch, poplar, maple, and spruce), the time of year harvested (summer versus winter), and the pharmaceutical extract processing procedures (fermented or unfermented). Commercially available extracts of mistletoe in Europe include ABNOBAviscum®, Cefalektin®, Eurixor®, Helixor®, Iscador®, Iscucin®, Isorel® and Lektinol®. Mistletoe extracts are one of the most frequently prescribed therapies for cancer in Europe, especially in Germany, Switzerland, and Austria.

Several biologically active substances are found in mistletoe extracts: lectins, viscotoxins, peptides, amino acids, flavonoides, oligo and polysaccharides, and other substances in low concentrations. Mistletoe extract has two mechanisms of action, tumor cytotoxicity and immunomodulation. The cytotoxic effects of mistletoe extract are a result of protein synthesis interference, cell cycle inhibition, and inducing apoptosis. The immunomodulatory properties of mistletoe extract work through increasing white blood cell numbers, as well as stimulating the production of immune enhancing cytokines, such as IL-1, IL-6, IFN $\gamma$ , TNF $\alpha$ . Lastly, mistletoe extract has been shown to have anti-angiogenic properties.

Mistletoe lectins are the most widely studied component of mistletoe extract. Four different lectins have been identified: ML-1, ML-2, ML-3, and *Viscum album* chitin-binding agglutinin. Lectins are composed of two subunits,  $\alpha$  and  $\beta$ , that when transported into the cell via endocytosis are dissociated from one another and can mediate different functions. The  $\alpha$  subunit has been shown to interfere with protein synthesis through ribosome-inactivation, therefore inducing apoptosis, while the sugar binding  $\beta$  subunit has been shown to have more immunomodulating characteristics, such as NK cell, lymphocyte, and macrophage activation. Similar to mistletoe lectins, viscotoxins, peptides, oligo and polysaccharides, and flavanoids have dual cytotoxic and immunostimulatory actions.

## 2.1 Helixor® M

Helixor® products are derived from three subspecies of white-berry mistletoe growing on different host trees: Helixor® A from fir mistletoe (abietis), Helixor® M from apple tree mistletoe (mali), and Helixor® P from pine mistletoe (pini). Helixor® M preparations have been recommended for lower abdomen (bladder, uterus, and ovaries), abdomen (stomach, colon, liver, pancreas), and breast cancers. Helixor® A preparations have been primarily used to treat head and neck cancers (including brain tumors), lung cancer, and prostate cancers, whereas Helixor® P preparations are recommended for malignant melanoma, sarcomas, kidney cancer, testicular cancer, and breast cancers.

Helixor® M was registered first in Germany in 1976 and got a marketing authorization according to the new German drug law in 1982. Besides Germany it has marketing authorization in Austria, Canada, Korea, Latvia, Lithuania, Luxemburg, Macedonia, Peru, Russia, Sweden and Switzerland. While mistletoe extracts are not approved for the treatment of cancer patients in the United States, *Viscum album* is listed in the United States Homeopathic Pharmacopoeia. It is estimated that Helixor® has been administered to over 400,000 patients since receiving marketing authorization.

Mistletoe products are currently registered exclusively for subcutaneous (SC) injection and are administered SC three times or twice a week or even daily. Other modes of administration like intracavitary instillation, intralesional injection or high-dose intravenous (IV) infusion are not yet registered, but are often used in clinics or hospitals for palliation in desperate cases after informed consent. There are 27 prospective or retrospective clinical trials investigating Helixor® in a total of 5,809 patients (colorectal, breast, lung and stomach cancer patients as well as patients with liver metastasis, malignant pleural effusions, chronic myeloid leukemia, malignant lymphoma and other cancer types). Systematic reviews confirm improvements in quality of life, tolerability of conventional tumor therapy, survival and/or tumor response.

Helixor® has been administered by intravenous infusion in some special indications since 1975. The main indication for Helixor® intravenous infusion therapy is reduced general condition as well as cancer pain in metastatic disease. The response to infusion therapy in this indication is much better than to standard subcutaneous treatment. In addition, patients with rapid deterioration of their quality of life may profit from this treatment. Tumor regression on high-dose infusion therapy has been demonstrated in some cases showing progressive disease in spite of subcutaneous Helixor® treatment. Among 33 cancer patients treated with high-dose Helixor® infusion, cancer response could be achieved in 9%, no-change in 36%, and a retardation of tumor progression in 27%, going along with a preserved quality of life for at least 6 months. Another study involving 60 cancer patients revealed a decline in ESR and tumor markers in 23% and 17%, respectively, which can be considered to be objective signs of clinical improvement. Given immediately before and during high-dose 5-FU chemotherapy, Helixor® infusion may result in an excellent tolerance of chemotherapy and in an improved quality of life. The clinical experience is largely based on treatment performed at Herdecke Community Hospital and Ludwig-Boltzmann-Institute for Clinical Oncology in Vienna, as well as the Havelhöhe Community Hospital in Berlin. A prospective clinical trial disclosed no evidence of acute or chronic toxicity in association with high-dose infusions of Helixor®.

Review of adverse drug reactions (ADRs) demonstrate that the IV infusion of Helixor® A or M to be safe with the most common reported symptoms to be allergic/pseudoallergic reactions

(generalized itching, tingling sensation, urticaria or exanthema, bronchospasm and Quincke's edema), as well as fever, chills, flu-like symptoms, fatigue, headache and infusion site inflammation. In an observational study recently published comparing ADRs associated with SC versus IV administration of various mistletoe extracts (including Helixor®), it was shown that the incidence of ADRs in patients that received IV mistletoe (4.6%) was lower than those receiving SC mistletoe (8.4%).

## **2.2 Rationale**

Toxicities associated with radiation and chemotherapy diminish quality of life for patients with advanced cancer. Nausea and vomiting, fatigue, mucositis, alteration in memory, and changes in appetite are common side effects with chemotherapy while, radiation can cause fatigue and skin changes. Systematic reviews of subcutaneous Helixor clinical studies confirm improvements in length and quality of life, tolerability of conventional tumor therapy, survival and/or tumor response. However, clinical studies on the efficacy of high-dose IV infusion of mistletoe products are not yet available. Until now, only a non-GCP compliant safety study on Helixor® IV infusion has been published preceded by a retrospective study Medical experience in the off-label use of Helixor® IV infusion. In the proposed phase I trial, we will seek to determine the safety and toxicity profile as well as the maximum tolerated dose of Helixor® M in patients with advanced solid tumors who have received at least one line of systemic therapy for metastatic disease. We anticipate this trial to be followed by disease-specific phase II trials in colon, pancreas, breast, bladder and/or any solid tumor subtypes where we see a clinical response.

## **3. ELIGIBILITY CRITERIA**

### **3.1 Inclusion Criteria**

- 3.1.1 Patients with advanced solid tumors and have received first line standard systemic therapy with chemotherapy, immunotherapy, hormonal therapy or other standard treatments for metastatic disease. Patients must either have progressed, are refractory, have stable disease and/or removed from therapy due to toxicities. Patients beyond first line therapy that do not meet criteria may be considered on a case by case basis and allowed at discretion of PI.
- 3.1.2 Patients with the presence of at least one measurable lesion as defined by RECIST 1.1 criteria for response assessment.
- 3.1.3 Age  $\geq 18$  years.
- 3.1.4 ECOG performance status 0-2 (**Appendix A**).
- 3.1.5 Life expectancy of greater than 3 months.

3.1.6 Patients must have normal organ and marrow function as defined below (without growth factor or transfusion support within 14 days prior to first dose of investigational product):

- WBC  $\geq 3,000/\text{mcL}$
- Absolute neutrophil count  $\geq 1,000/\text{mcL}$
- Platelets  $\geq 90,000/\text{mcL}$
- Hemoglobin  $\geq 9.0 \text{ g/dL}$
- Total bilirubin  $\leq 1.5 \text{ X ULN}$  (patients with diagnosed Gilbert's Syndrome will not be excluded if their direct bilirubin is within normal institutional limits)
- AST(SGOT)/ALT(SGPT)  $\leq 2.5 \text{ X ULN}$
- Creatinine  $\leq 1.5 \text{ x ULN}$  OR creatinine clearance  $\geq 50 \text{ mL/min/1.73 m}^2$

3.1.7 Female patient of childbearing potential has a negative urine or serum pregnancy test. If the urine test is positive or cannot be confirmed as negative, a serum pregnancy test will be required. The serum pregnancy test must be negative for the patient to be eligible.

3.1.8 Female patients enrolled in the study, who are not free from menses for >2 years, post hysterectomy / oophorectomy, or surgically sterilized, must be willing to use either 2 adequate barrier methods *or* a barrier method plus a hormonal method of contraception to prevent pregnancy or to abstain from heterosexual activity throughout the study, starting with Visit 1 through 28 days after the last dose of study therapy. Approved contraceptive methods include for example; intra uterine device, diaphragm with spermicide, cervical cap with spermicide, male condoms, female condoms with spermicide, or oral contraceptives. Spermicides alone are not an acceptable method of contraception.

Male patients must agree to use an adequate method of contraception starting with the first dose of study drug through 28 days after the last dose of study therapy.

3.1.9 Ability to understand and the willingness to sign a written informed consent document.

## 3.2 Exclusion Criteria

3.2.1 Patient with a known history or evidence of brain metastases.

3.2.2 Patients who have had chemotherapy, radiation, hormonal, or biological cancer therapy within 28 days prior to the first dose of study drug excluding patients on long term hormonal therapies who have been on a stable dose for at least 3 months.

- 3.2.3 Patient is currently participating or has participated in a study of an investigational agent or using an investigational device within 28 days of the first dose of study drug.
- 3.2.4 Patients who have had surgery within 28 days of dosing of investigational agent, excluding minor procedures (dental work, skin biopsy, etc), celiac plexus block, and biliary stent placement.
- 3.2.5 Patient is expected to require any other form of systemic or localized antineoplastic therapy while on study.
- 3.2.6 Patient who has had prior treatment with Mistletoe.
- 3.2.7 Patients who have received systemic corticosteroids within 28 days prior to the first dose of study drug. Note: Systemic steroid therapy is allowed for subjects on replacement therapy as long as prednisone  $\leq$  10 mg or its steroid equivalent.
- 3.2.8 Patients who have received systemic NSAID therapy within 14 days prior to the first dose of study drug.
- 3.2.9 History of allergic reactions attributed to compounds of similar chemical or biologic composition to Mistletoe.
- 3.2.10 Uncontrolled intercurrent illness including, but not limited to, ongoing or active infection, symptomatic congestive heart failure, unstable angina pectoris, cardiac arrhythmia, or psychiatric illness/social situations that would limit compliance with study requirements.
- 3.2.11 Presence of  $\geq$  CTCAE grade 2 toxicity (except peripheral neuropathy and ototoxicity, which are excluded if  $\geq$  CTCAE grade 3) due to prior cancer therapy.
- 3.2.12 Autoimmune disease: Patients with a history of inflammatory bowel disease, including ulcerative colitis and Crohn's Disease, are excluded from this study, as are patients with a history of symptomatic disease (*e.g.*, rheumatoid arthritis, systemic progressive sclerosis [scleroderma], systemic lupus erythematosus, autoimmune vasculitis [*e.g.*, Wegener's Granulomatosis]); CNS or motor neuropathy considered of autoimmune origin (*e.g.*, Guillain-Barre Syndrome and Myasthenia Gravis, multiple sclerosis). History of Grave's disease on stable thyroid hormone replacement for at least 1 year is allowed.
- 3.2.13 Patients with a known history of HIV, hepatitis B, hepatitis C, or tuberculosis infection. Patients with a history of cleared hepatitis C (undetectable viral loads) are allowed.
- 3.2.14 Women with a positive pregnancy test on enrollment or prior to investigational product administration

3.2.15 Women who are pregnant or breastfeeding.

3.2.16 Sexually active fertile men not using effective birth control if their partners are of child bearing potential.

3.2.17 Patient is unwilling or unable to comply with study procedures.

### **3.3 Inclusion of Women and Minorities**

Both men and women of all races and ethnic groups are eligible for this trial.

## **4. REGISTRATION PROCEDURES**

### **4.1 General Guidelines**

Eligible patients will be entered on study centrally at the Sidney Kimmel Comprehensive Cancer Center at the Johns Hopkins University by the Lead Study Coordinator. All sites should contact the Lead Study Coordinator at [[contact]](mailto:[contact]) to verify ongoing study enrollment. The Registration Form and Eligibility Worksheet will be supplied to each participating site.

If a patient does not receive protocol therapy following registration, the patient's registration on the study may be canceled. The Study Coordinator should be notified of cancellations as soon as possible.

### **4.2 Registration Process**

To register a patient, the following documents should be completed and sent to the Protocol Chair and Lead Study Coordinator at the Coordinating Center at [[contact]](mailto:[contact]):

- Registration Form
- Signed patient consent/HIPAA authorization form
- Eligibility Screening Checklist
- Copy of required screening tests and scans

To complete the registration process, the Coordinating Center Lead Study Coordinator will:

- Assign a patient study number
- Register the patient on the study
- E-mail the Registration Form back to the participating site

## **5. TREATMENT PLAN**

### **5.1 Agent Administration**

Treatment will be administered on an outpatient basis. Reported adverse events and potential risks are described in **Section 7**. Appropriate dose modifications are described in **Section 6**. No investigational or commercial agents or therapies other than those described

below may be administered with the intent to treat the patient's malignancy.

| REGIMEN DESCRIPTION |                                                                                                                                        |                         |                  |                 |
|----------------------------|----------------------------------------------------------------------------------------------------------------------------------------|-------------------------|------------------|-----------------|
| Agent               | Premedications; Precautions                                                                                                     | Dose             | Route     | Schedule |
| Helixor® M          | No prophylactic pre-medication will be given unless indicated by previous experience in an individual patient per Section 5.5 . | Per assigned dose level | IV over 3 hours* | M, W, F         |

\* Infusion times are approximate ( +/- 15min) and may need to be adjusted based on patient tolerability

| Dose Level | # Patient | Dose of Helixor® M (mg) |          |          |                          |          |          |
|-------------------|------------------|--------------------------------|----------|----------|--------------------------|----------|----------|
|                   |                  | Week 1                  |          |          | Week 2 and beyond |          |          |
|                   |                  | M                       | W | F | M                 | W | F |
| 1                 | 1-6              | 50                             | 150      | 150      | 150                      | 150      | 150      |
| 2                 | 1-6              | 50                             | 300      | 300      | 300                      | 300      | 300      |
| 3                 | 1-6              | 50                             | 600      | 600      | 600                      | 600      | 600      |
| 4                 | 1-6              | 50                             | 900      | 900      | 900                      | 900      | 900      |
| 5                 | 1-6              | 50                             | 1200     | 1200     | 1200                     | 1200     | 1200     |
| 6                 | 1-6              | 50                             | 1500     | 1500     | 1500                     | 1500     | 1500     |
| 7                 | 1-6              | 50                             | 1800     | 1800     | 1800                     | 1800     | 1800     |
| 8                 | 1-6              | 50                             | 2000     | 2000     | 2000                     | 2000     | 2000     |

Helixor® M will be administered intravenously according to the schedule shown above. The patient must be observed in the clinic for at least 30 minutes after the lead in dose and the first dose of the assigned dose level. Vital signs will be collected prior to each dose. Acute reactions will be managed using guidance located in **Section 5.5** and standard therapy for acute drug reactions as per institutional standard of care and reported to the sponsor.

## 5.2 Dosing Criteria

The following dosing criteria must be met prior to the first dose each week after Week 1:

- ANC  $\geq 1,000/\text{mcL}$
- Platelets  $\geq 90,000/\text{mcL}$
- Hemoglobin  $\geq 8 \text{ g/dL}$
- Total bilirubin  $\leq 1.5 \times \text{ULN}$  (patients with diagnosed Gilbert's Syndrome, direct bilirubin should be within normal institutional limits)
- AST(SGOT)/ALT(SGPT)  $\leq 2.5 \times \text{ULN}$
- Creatinine  $\leq 1.5 \times$  institutional upper limit of normal or creatinine clearance  $\geq 50 \text{ mL/min/1.73 m}^2$

## 5.3 Contraception, Use in Pregnancy, Use in Nursing

### 5.3.1 Contraception

Helixor® M may have adverse effects on a fetus *in utero*. Furthermore, it is not known if Helixor® M has transient adverse effects on the composition of sperm. Non-pregnant, non-breast-feeding women may be enrolled if they are considered highly unlikely to conceive. Highly unlikely to conceive is defined as 1) surgically sterilized, or 2) postmenopausal (a woman who is  $\geq 45$  years of age and has not had menses for greater than 2 years will be considered postmenopausal), or 3) amenorrheic for  $< 2$  years without a hysterectomy and oophorectomy, or 4) not heterosexually active for the duration of the study, or 5) heterosexually active and willing to use a method of birth control (which is also required for the female partners of male patients). Birth control methods can be either a barrier method or a hormonal method to prevent pregnancy, used throughout the study starting with Visit 1 through 28 days after the last dose of study medication. Male patients enrolled in this study must also agree to use an adequate method of contraception starting with Visit 1 through 28 days after the last dose of study drug.

The following are considered adequate barrier methods of contraception: diaphragm, condom (by the partner), copper intrauterine device, sponge, or spermicide. Appropriate hormonal contraceptives will include any registered and marketed contraceptive agent that contains an estrogen and/or a progestational agent (including oral, subcutaneous, intrauterine, or intramuscular agents).

Patients should be informed that taking the study medication may involve unknown risks to the fetus (unborn baby) if pregnancy were to occur during the study. In order to participate in the study they must adhere to the contraception requirement (described above) for the duration of the study. If there is any question that a patient will not reliably comply with the requirements for contraception, that patient should not be entered into the study.

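### Section 5.3.1 sets a weaker contraception rule for women than inclusion criterion 3.1.8 over the same period; a minor second slip is the reversed grade sign in Section 5.6

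*Protocol*

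**What the plan says.** **Protocol, Section 3.1, criterion 3.1.8.** It applies to female patients "who are not free from menses for >2 years, post hysterectomy / oophorectomy, or surgically sterilized", where the opening negative governs all three conditions. These women "must be willing to use either 2 adequate barrier methods", or a barrier plus a hormonal method, or abstain from heterosexual activity. The undertaking runs from Visit 1 through 28 days after the last dose. Spermicide alone is ruled out.

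**Protocol, Section 5.3.1.** It opens with a permission: "Non-pregnant, non-breast-feeding women may be enrolled if they are considered highly unlikely to conceive". Five alternatives joined by *or* then define that phrase:

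1. surgically sterilized;
2. postmenopausal, meaning aged 45 or over with no menses for more than 2 years;
3. amenorrheic for less than 2 years (the text of this route and the next reads "years without a hysterectomy and oophorectomy, or 4) not heterosexually active for the duration of the study");
4. not heterosexually active, as in that quote;
5. "heterosexually active and willing to use a method of birth control".

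The rule for the method follows: "Birth control methods can be either a barrier method or a hormonal method to prevent pregnancy", again from Visit 1 through 28 days after the last dose. Then comes the list of what counts: "The following are considered adequate barrier methods of contraception: diaphragm, condom (by the partner), copper intrauterine device, sponge, or spermicide". The section makes its own rule a condition of taking part: "In order to participate in the study they must adhere to the contraception requirement (described above) for the duration of the study".

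**Protocol, Sections 5.6 and 6.1.** One bullet in 5.6 ends treatment when a delay of more than 2 weeks is caused by drug-related toxicity that has not resolved to ≥ grade 1 or baseline. Section 6.1 gives the rule for the same event with ≤ grade 1. Section 5.8 makes the 5.6 list the criteria for removal from study.

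**The concern.** Sections 5.3.1 and 5.3.2 both say that the drug may have adverse effects on a fetus, so the contraception rule is a safety rule. The protocol states it twice, at different strengths, and does not say which statement prevails. A woman using one method, or amenorrheic for under 2 years and using none, complies with 5.3.1 and fails 3.1.8. This is a multi-center study, so one site could counsel from 3.1.8 and another from 5.3.1, and each would be following the printed text.

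The 5.6 bullet is a lesser matter of the same kind: a safety rule that contradicts its counterpart and, read literally, does not do its job.

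**Working it through.** No arithmetic applies and the plan gives no figure to reproduce. The check sets the two contraception rules side by side and then the two stopping rules.

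**Contraception: each 5.3.1 route against 3.1.8**

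| Route in 5.3.1 | 5.3.1 requires | 3.1.8 requires of the same woman | Agree? |
|---|---|---|---|
| 1. Sterilized | nothing further | nothing (outside its scope) | yes |
| 2. Postmenopausal, aged 45 or over | nothing further | nothing (free from menses for more than 2 years) | yes; the age condition makes 5.3.1 the stricter text |
| 3. Amenorrheic for under 2 years | 0 methods | 2 methods or abstinence | **no** |
| 4. Not heterosexually active | abstinence | abstinence is accepted | yes |
| 5. Heterosexually active, using birth control | 1 method, barrier or hormonal | 2 methods (two barrier, or barrier plus hormonal) | **no** |

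*Route 3.* A woman amenorrheic for under 2 years has not been free from menses for more than 2 years. The route itself describes her as without a hysterectomy and oophorectomy. Unless she is sterilized, in which case route 1 applies, she falls inside 3.1.8. Only route 5 mentions birth control, so route 3 as printed asks none of her.

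*Route 5.* One barrier method is enough and spermicide is listed as an adequate barrier method. Spermicide alone therefore satisfies 5.3.1, and 3.1.8 rejects exactly that. This follows from the one-method rule and is not a separate conflict: 3.1.8 does not bar spermicide as one of two methods.

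*Period.* Both texts run from Visit 1 through 28 days after the last dose, so they compete over the same interval.

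Two of the five routes conflict. That counts list items; the documents give no basis for the number of women affected.

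**Stopping for unresolved toxicity: 5.6 against 6.1**

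| Toxicity after 2 weeks of delay | 5.6 as printed (stop unless ≥ grade 1 or baseline) | 6.1 (stop unless ≤ grade 1 or baseline) |
|---|---|---|
| Persists at grade 2, 3 or 4, above baseline | grade is ≥ 1, so the bullet is not met: no stop | grade is not ≤ 1: stop |
| Down to grade 1 | not met: no stop | resolved: no stop |

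The 5.6 bullet fails to fire in the very case it is for, so the sign is reversed. Section 5.7 also uses ≤ grade 1, but it governs safety follow-up after discontinuation. The true comparator is 6.1.

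**The case against.** The strongest reply is that an inclusion criterion governs. Criterion 3.1.8 is mandatory, whereas the opening of 5.3.1 is permissive. A woman who fails 3.1.8 is ineligible whatever 5.3.1 says. Section 4.2 requires an eligibility checklist at registration, Section 12.3 has the Protocol Chair monitor eligibility at all sites, and 5.3.1 itself ends by keeping out any patient whose compliance with contraception is in doubt. Most of this stands, and it makes wrongful enrolment unlikely. It does not remove the conflict. The protocol gives no order of precedence, and 5.3.1 ties participation to the requirement described above, which within that section most naturally means the weaker rule. The pregnancy tests in the Section 10 calendar detect a pregnancy; they do not prevent exposure.

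A reader might infer that 3.1.8 acts only at entry, leaving the weaker rule in sole charge on study. The text does not support this, because the 3.1.8 undertaking itself extends through 28 days after the last dose.

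It can also be said that route 3 is merely garbled. Perhaps so, but as printed it exempts women whom 3.1.8 covers.

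On the sign, the reply is that 5.6 is an obvious slip with the right rule in 6.1. That is correct, and it is why this part is minor. A reader might infer that patients with persisting grade 2–4 toxicity would be kept on treatment. The documents do not support that: 6.1 stops them, 6.2 stops therapy at a third occurrence of the same toxicity requiring interruption, and other 5.6 bullets (DLT, grade 3 or 4 hypersensitivity, the investigator's judgment) remain available.

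**Conclusion.** The contraception conflict is real and should be corrected. Section 5.3.1 asks for one method where 3.1.8 asks for two, and for none from women amenorrheic for under 2 years, over an identical period. The consequence is two operative rules of unequal strength for a drug with a stated possible fetal risk. The documents do not show that any woman has been or would be wrongly enrolled, nor that 5.3.1 overrides 3.1.8.

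This rests on reading the five routes as alternatives, as printed, and on taking the requirement described above to mean that of 5.3.1. The consent pages are not available, so whether they repeat the 5.3.1 text is unknown.

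The 5.6 sign is a plain misprint with small practical effect. Both points concern safety wording only and leave the DLT and MTD definitions, the sample size and the analysis untouched.

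**What to change.** In Section 5.3.1:

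- replace the one-method rule with that of 3.1.8: two barrier methods, or a barrier plus a hormonal method, or abstinence;
- delete the route for amenorrhea of under 2 years;
- state that spermicide alone is not acceptable.

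A cross-reference to 3.1.8 in place of a second statement of the rule would keep the two from drifting apart again. Correct the consent form if it repeats the 5.3.1 text.

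In Section 5.6, change the sign in the bullet on delays over 2 weeks to ≤ grade 1 or baseline, as in 6.1.

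The cost is an amendment to wording, and to the consent form if it is affected. Visits, sample size and analysis do not change.
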